**Methods and analysis:**

Here, we will evaluate the clinical use of tolDC in a well-defined population of MS patients in two phase I clinical trials. In doing so, we aim to compare two ways of tolDC administration, namely intradermal and intranodal. The cells will be injected at consecutive intervals in three cohorts receiving incremental doses of tolDC, according to a best-of-five design. The primary objective is to assess the safety and feasibility of tolDC administration. For safety, the number of adverse events including MRI and clinical outcomes will be assessed. For feasibility, successful production of tolDC will be determined. Secondary endpoints include clinical and MRI outcome measures. The patients’ immune profile will be assessed to find presumptive evidence for a tolerogenic effect in vivo.

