## Methods and analysis

### Study design

Two open-label, dose-escalation phase I clinical trials, MS-tolDC and TOLERVIT-MS, are designed in a coordinated and comprehensive manner and run simultaneously in Belgium (Antwerp University Hospital, Edegem) and Spain (Hospital Germans Trias i Pujol, Badalona), respectively. Patient recruitment started mid-2017 and is anticipated to end in 2020.

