### Study population

#### Eligibility and enrolment

Patients with active relapsing-remitting and active progressive MS, diagnosed according to most recent McDonald criteria,^39 40^ and who are not eligible for or do not want to be treated with currently available DMT, will be recruited. Patients are included after written informed consent and enrolled in the study when the inclusion and exclusion criteria are met (table 2).

**Table 2 T2:** Inclusion and exclusion criteria. All the inclusion criteria must be fulfilled. The presence of any of the exclusion criteria shall exclude the patient

Inclusion criteria	Exclusion criteria
MS according to most recent McDonald criteria	Previous use of immunosuppressive or cytostatic treatment, including mitoxantrone, cladribine, alemtuzumab or bone marrow transplantation or stem cell transplantation at any time prior to enrolment
Age 18–60 years	Treatment with fingolimod or natalizumab or dimethylfumarate in the past 12 weeks or teriflunomide within the past 15 weeks or ocrelizumab/rituximab within the past 6 months prior to the first administration
EDSS of 0–6.5 inclusive	Pregnancy or planning pregnancy in the next 12 months and breast feeding
First signs or symptoms at least 3 months prior to enrolment in the study	Drug or alcohol abuse
Active MS (relapsing and/or progressive): one relapse in the past year and/or at least one enhancing lesion on brain MRI in the past year; at least one new or enlarging T2 lesion in comparison with a reference scan from maximum 1 year before	Inability to undergo MRI assessments
Normal peripheral B-cell count after treatment with ocrelizumab	
No evidence of relapse for at least 30 days prior to start of screening and throughout during the screening phase	History of or actual signs of immunodeficiency or malignancies
Positive T cell reactivity response to a mix of seven myelin-derived peptides	Concurrent clinically relevant cardiac, immunological, pulmonary, neurological, renal or other major disease
Able to sign informed consent and comply with the protocol assessments	Active or chronic infection (hepatitis B or C, HIV, syphilis or tuberculosis)
No wish to be treated with currently available DMT	Splenectomy
Appropriate venous access and *adequate cervical lymph nodes on ultrasound mapping	

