#### Determination of sample size and dose-escalation procedure

The studies will be conducted according to a ‘best of five’ design,^41^ an alternative of the traditional 3+3 design in that one additional patient is added when one or even two dose-limiting toxicities (DLT) are observed among the first three patients. Another patient is added when two DLT are observed among four treated patients. Dose escalation is allowed if DLT are observed among none of three, one of four or two of five patients, but the trial will terminate if three or more DLT are observed. A DLT is defined as a serious adverse event (SAE) that is attributable to the study cells administered, or of which the severity prevents further escalation. Dose escalation decisions will be made after all subjects in the cohort have completed at least 3 months of follow-up and when the results of the safety and tolerability analyses of the preceding dose regimen are satisfactory in the judgement of the investigators and the independent Data Safety Monitoring Board (DSMB).

An overview of the dose escalation is provided in table 3. Altogether, each phase I study is intended to accrue a total number of 9–15 evaluable patients.

**Table 3 T3:** Outline of the cell doses and patient numbers, per phase I clinical trial, in the dose escalation cohorts for intradermal and intranodal administration of tolDC

Cohort	Treatment regimen	Patient numbers
1	6 i.d./i.n. injections of 5×10^6^ tolDC	N=3 (+1+1)
2	6 i.d./i.n. injections of 10×10^6^ tolDC	N=3 (+1+1)
3	6 i.d./i.n. injections of 15×10^6^ tolDC	N=3 (+1+1)

N, number; i.d., intradermal; i.n., intranodal; tolDC, tolerogenic dendritic cells.

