### Analysis

Given the design of the study (phase I) and its specific primary end point (safety), no confirmatory statistical testing will be performed. P-values will be calculated but interpreted with caution. Study investigations will be exploratory and conclusions will be based on the complete set of patient evidence.

Analyses of safety variables will be performed with the safety population (all the patients treated with at least one dose of the cell product) by available data only analysis. For demographic and safety analysis, that is, the incidence of AE, laboratory values and changes in vital signs, descriptive statistics will be calculated including frequencies for categorical variables and mean and SD, or median and IQR for quantitative parameters. In brief, EDSS and other repeatedly measured variables will be analysed by means of Mixed Models for Repeated Measurements. In case model assumptions are violated (eg, non-Gaussian errors) or when dealing with ordinal efficacy variables, alternative methods (including non-parametric methods and ordinal regression methods for repeated measurements) will be used. The percentage of patients with 1-point in EDSS improvement will be estimated using a binomial regression model including the treatment and the baseline EDSS. The remainder of variables will be analysed according to the appropriate statistical test: χ^2^ or Fisher’s exact test to compare categorical variables, the dependent or independent t-test for continuous Gaussian-distributed variables and the Wilcoxon or Mann-Whitney test for ordinal and non-Gaussian continuous data. The significance level alpha will be set at 0.05 for two-tailed analysis. Variables to assess the analysis of secondary and tertiary outcome measures will be performed with per protocol population. Continuous variables as a minimum will be described by number of total and non-missing observations (n) and the appropriate location-scale statistics including arithmetic mean, SD, minimum, median, Q1–Q3 and maximum. Categorical variables will be presented using the number of non-missing observations (n) or the number of patients in the population (N) as applicable and percentages (%). Two-sided 95% (exact) CI will be provided when relevant.

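### The model for EDSS improvement includes a treatment term that neither trial can support: it is constant within a trial, and as a dose-cohort factor it would probably have no finite maximum-likelihood fit

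*Protocol article*

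**What the plan says.** The Analysis section names an endpoint, a model and its terms: "The percentage of patients with 1-point in EDSS improvement" "will be estimated using a binomial regression model including the treatment and the baseline EDSS". It does not say what the treatment term codes, or whether the two trials are pooled for this model.

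The design is given elsewhere in the protocol article:

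- Study design: "Two open-label, dose-escalation phase I clinical trials, MS-tolDC and TOLERVIT-MS". No control arm is described.
- Table 3: three cohorts of 3 to 5 patients, differing only in cell dose. Cohort 1, for example, receives "6 i.d./i.n. injections of 5×10^6^ tolDC".
- Determination of sample size: "each phase I study is intended to accrue a total number of 9–15 evaluable patients".
- Abstract: "we aim to compare two ways of tolDC administration, namely intradermal and intranodal". Each trial uses one route, and the strengths and limitations box concedes that patients are not randomised between the trials.
- Table 2: "EDSS of 0–6.5 inclusive" is an inclusion criterion, so patients with no measurable disability may enter.

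The Analysis section also provides for counts and percentages for categorical variables, and for exact 95% intervals where relevant. It assigns secondary outcomes to the per-protocol population.

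**The concern.** A treatment term in a regression needs at least two treatment levels, each with some patients who improve and some who do not. Every patient here receives tolDC, so the obvious comparison does not exist. The other codings leave very small groups or a comparison across non-randomised trials. When a small group contains no improver (or only improvers), the likelihood has no finite maximum. Software then prints huge coefficients with huge standard errors, or reports non-convergence. The plan promises p-values, and a Wald p-value from such a fit carries no information. The alternative methods named in the Analysis section are attached to the repeated-measures models, so no fallback is tied to this one.

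**Working it through.** **The plan's own figure.** 3 cohorts × 3 = 9 and 3 cohorts × 5 = 15, which reproduces the stated 9–15 per trial. The plan gives no expected improvement rate p. I assume 10%, 20% and 30%, and show 5% and 50% as extremes.

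**Reading 1: treated versus not treated.** The treatment column equals the intercept column. The design matrix with intercept, treatment and baseline EDSS has rank 2 out of 3, so the treatment coefficient is not identifiable. The percentage still is. A before/after coding does not help, because improvement is itself a change from baseline.

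**Reading 2: dose cohort as a three-level factor.** With m patients per cohort, independent at rate p, the probability that at least one cohort is all-improved or all-unimproved is

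1 − [1 − (1−p)^m − p^m]^3.

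- m = 3: p = 10%: 1 − (1 − 0.729 − 0.001)^3 = 1 − 0.27^3 = 98.0%. p = 20%: 1 − 0.48^3 = 88.9%. p = 30%: 1 − 0.63^3 = 75.0%.
- m = 5: p = 10%: 1 − 0.4095^3 = 93.1%. p = 20%: 1 − 0.672^3 = 69.7%. p = 30%: 1 − 0.8295^3 = 42.9%.

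Any such cohort rules out a finite maximum-likelihood estimate, so these are floors. Adding baseline EDSS can only raise them.

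**With baseline EDSS in the model.** I simulated 1,500 trials per setting (logit link) and checked complete or quasi-complete separation by linear programming. The simulation standard error is at most √(0.25/1500) = 1.3 points. Two assumptions on baseline EDSS were used: uniform on 1.0–6.5, or uniform on 0–6.5 with improvement impossible below 1. The table gives the percentage of trials without a finite fit at p = 10% / 20% / 30%.

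| Coding | EDSS 1.0–6.5 | EDSS 0–6.5 | Range over all runs |
|---|---|---|---|
| Cohort factor, 3 per cohort | 98.5 / 90 / 78 | 99 / 93 / 82 | about 99 / 89–94 / 77–82 |
| Cohort factor, 5 per cohort | 94 / 70 / 44 | 95 / 77 / 55 | about 95 / 70–77 / 41–55 |
| Route, pooled, 9 v 9 | 61 / 25 / 9 | 67 / 35 / 13 | 61–69 / 25–35 / 7–16 |
| Route, pooled, 15 v 15 | 37 / 7 / 1 | 45 / 10 / 3 | 37–45 / 7–11 / 1–3 |

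The 41% lies just below the exact floor of 43%, so 43% is the better lower end. At p = 5% and 50%, the cohort factor (EDSS 1.0–6.5) fails in 99.8% and 61% of trials at N = 9, and in 98.8% and 19% at N = 15. Dose as a linear term fails in 76 / 51 / 31% at N = 9 and 54 / 22 / 6% at N = 15.

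**What a separated fit returns.** Take improvers 0/3, 1/3 and 1/3 in the three cohorts (N = 9). The two cohort coefficients come out at about 21 with standard errors of about 16,600, so z ≈ 21/16,600 ≈ 0.001. The baseline EDSS slope stays finite (−0.31, SE 0.58). The mean fitted percentages are 0%, 33% and 33%, and overall 22.2%, which is the observed 2/9.

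**Baseline EDSS below 1.** Each such patient lowers the highest attainable percentage by 1/9 = 11 points at N = 9 or 1/15 = 7 points at N = 15.

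**The case against.** Four points can be made in the plan's favour.

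1. *The named quantity survives.* A reader might infer that the estimate itself becomes infinite or undefined. The documents do not support that. The plan asks for a percentage, and the fitted percentage stays between 0 and 1 even under separation. The equality with the observed proportion was shown for a logit link, which the plan does not specify. What fails is the inference built on the model, not the point estimate.

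2. *A descriptive route already exists.* A reader might also infer that the regression is the only analysis available for this endpoint. It is the only estimation method named for it, but the general provisions on percentages and exact intervals cover a yes/no variable. This stands, and it makes the change easy. Those provisions are not named as a substitute when the model fails.

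3. *An article condenses.* Coding, link function and pooling are normally left to the full protocol or SAP, and their absence is no fault. The difficulty is that the article does state the terms. Each coding that the design allows is not identifiable, probably separated, or a comparison of routes without randomisation. More detail would select among these without removing the problem.

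4. *The rates are assumed and the stakes low.* Failure is likely, not certain: with 15 per route pooled and improvement of 20% or more, the model usually fits. No confirmatory test is planned, safety and feasibility are primary, and dose escalation does not use EDSS improvement. All of this stands and limits the consequence.

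On patients with low baseline EDSS, a reader might infer that the percentage will be materially diluted. The plan gives no baseline distribution, so the number of such patients is unknown and may be zero.

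**Conclusion.** The point holds in a limited form. The treatment term has no identifiable coefficient within a trial if it means treated versus not treated. If it means dose cohort, a finite fit is improbable at 9 patients for every rate tried (61% to 99.8% failures), and at 15 patients for rates up to about 20%. Pooled route is a lesser problem numerically but not a randomised comparison. In a failed fit the only usable estimate of the percentage is the raw proportion, without a usable model-based interval or test for the separated cohorts.

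These sizes rest on assumed improvement rates, an assumed baseline EDSS distribution and no true covariate effects. A real effect of baseline EDSS would tend to make separation more frequent, as would losing patients from the per-protocol set. Because the outcome is exploratory and secondary, this is a modest but worthwhile correction.

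**What to change.** Replace the regression sentence. For each trial, report the number and percentage of patients with a 1-point EDSS improvement as x/N with the exact (Clopper-Pearson) 95% CI, by dose cohort and overall, and drop the treatment term.

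State how many patients had baseline EDSS below 1, and give the percentage among those with baseline EDSS of at least 1 alongside the percentage in all patients.

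If a model is still wanted, use Firth or exact logistic regression on baseline EDSS. Ordinary maximum likelihood with EDSS alone still fails in 51 / 27 / 13% of trials at N = 9 for rates of 10 / 20 / 30%. If no patient improves (0.9^9 = 39% of trials at N = 9 and a 10% rate), no model can say anything about baseline EDSS.

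The cost is a few sentences in the Analysis section and intervals that look wide: 1/9 gives 0.3% to 48%, 3/15 gives 4.3% to 48%, and a cohort with 0/3 gives 0 to 1 − 0.025^(1/3) = 71%. That width reflects what so few patients can show.

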### Primary outcome measures

#### Safety

To evaluate the safety of administered tolDC, occurrence of AE will be recorded using clinical outcome measures, that is, physical (skin, pain and adenopathies) and neurological examination (relapses and worsening disability) and non-clinical outcome measures, that is, brain MRI, biochemical and haematological safety. The frequent MRI monitoring will allow us to monitor the safety of tolDC in MS patients objectively by measuring T1-enhancing lesions and new and/or enlarging T2 lesions. In this way, unexpected disease activity can be detected timely. The severity of AE will be defined according to the WHO toxicity grading scale. The relationship of an AE to the investigational product will be determined by the neurologists and the independent DSMB on the basis of their clinical judgement.

A proportion of the patients may experience MS relapses during the study. A relapse is defined as a new or worsening neurological symptom that occurs in the absence of fever or infection, occurs at least 30 days following the onset of a previous relapse, persists for at least 24 hours and includes an increase in Expanded Disability Status Scale (EDSS) score^42^ from the previous assessment matching one of the following: (i) an increase of ≥1 on the total scale score; or (ii) an increase of ≥2 points on one of the appropriate Functional System Scores (FSS) or (iii) an increase of >1 point on two or more of the appropriate FSS. Patients will be instructed to notify their neurologist as soon as possible but within 72 hours the latest and will be examined within 7 days of onset of the symptoms. In case of an MS relapse, a course of high-dose steroids can be administered at the discretion of the treating neurologist.

Study treatment must be discontinued for a given patient if the investigator determines that continuing would result in a significant risk for that patient. In case of terminating the study treatment, patients will still be monitored for safety issues for the duration of the study.

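### Secondary disability, MRI and immune outcomes are analysed only per protocol, so in 9–15 uncontrolled patients a few outcome-related exclusions can shift the efficacy summaries towards benefit

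*Protocol article*

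**What the plan says.** The Analysis section assigns populations by type of outcome. For safety: "Analyses of safety variables will be performed with the safety population", defined as the "safety population (all the patients treated with at least one dose of the cell product) by available data only analysis". For everything below the primary outcome, analysis of "secondary and tertiary outcome measures will be performed with per protocol population". No second population is named for the latter group, and the article does not define per protocol.

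The secondary outcomes in question are:

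- the proportion free from disability progression, based on EDSS, T25FW and 9-HPT, with SDMT change also recorded (Clinical evaluation);
- change in enhancing lesions, new or enlarging T2 lesions, T2 lesion load and brain volume (MRI acquisition and evaluation);
- immune profile and myelin-specific T cell reactivity (Immune-monitoring).

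MSQOL-54 has its own heading. The article labels no outcome as tertiary.

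The Safety section under Primary outcome measures says: "Study treatment must be discontinued for a given patient if the investigator determines that continuing would result in a significant risk for that patient". It adds: "In case of terminating the study treatment, patients will still be monitored for safety issues for the duration of the study". The same section lists as safety measures "neurological examination (relapses and worsening disability) and non-clinical outcome measures, that is, brain MRI, biochemical and haematological safety", and names T1-enhancing and new or enlarging T2 lesions as what the MRI will count.

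**The concern.** Membership of a per protocol set depends on what happens after treatment starts. Here a patient must come off treatment when the investigator sees significant risk. In a trial that scans often in order to catch unexpected disease activity, some of those patients may also be the ones who are worsening. If they leave the analysis set, disability and MRI results are summarised in the patients who did better. There is no control arm in which a similar loss could be seen, and each trial is small.

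These summaries will be used. Secondary objectives says that all secondary objectives contribute to proof of principle, and the Discussion says that the results of the two trials will select dose and route for phase II. If exclusions differ by dose or route, that choice is affected as well.

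Disability worsening and lesion counts also appear twice, as safety measures (all treated) and as secondary outcomes (per protocol). The article does not say which of the two results leads.

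**Working it through.** **Plan's own figure.** Table 3 has three cohorts of 3 (+1+1) patients. The minimum is 3 × 3 = 9 and the maximum 3 × 5 = 15. This reproduces the stated 9–15 evaluable patients per trial. The article gives no event rate, discontinuation rate or power calculation, so the rates below are assumptions. N = 9 and N = 15 are taken as the numbers treated.

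**Step 1: observed shift.** With N treated, f progression-free and k progressors excluded, the proportion is f/N in all treated and f/(N − k) per protocol. Assume 3 progressors. Exact (Clopper-Pearson) 95% intervals are in brackets.

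| | All treated | 1 progressor excluded | 2 progressors excluded |
|---|---|---|---|
| N = 9 | 6/9 = 66.7% (29.9–92.5) | 6/8 = 75.0% (34.9–96.8) | 6/7 = 85.7% (42.1–99.6) |
| N = 15 | 12/15 = 80.0% (51.9–95.7) | 12/14 = 85.7% (57.2–98.2) | 12/13 = 92.3% (64.0–99.8) |

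One exclusion adds 8.3 points (N = 9) or 5.7 points (N = 15). Two add 19.0 or 12.3 points. The intervals overlap widely. The shift lies within sampling error, but unlike sampling error it has a direction.

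**Step 2: expected shift.** Let p be the true progression rate, and a and b the probabilities of exclusion with and without progression. The expected per protocol proportion progression-free is

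(1 − p)(1 − b) / [(1 − p)(1 − b) + p(1 − a)].

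With p = 0.3 the true value is 70.0%:

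- a = b = 0.25: 0.7 × 0.75 / (0.7 × 0.75 + 0.3 × 0.75) = 70.0%, shift 0.
- a = 0.25, b = 0.05: 0.665 / (0.665 + 0.225) = 74.7%, shift +4.7 points.
- a = 0.50, b = 0.05: 0.665 / (0.665 + 0.150) = 81.6%, shift +11.6 points.
- a = 0.75, b = 0.05: 0.665 / (0.665 + 0.075) = 89.9%, shift +19.9 points.

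The shift is towards benefit only when a exceeds b.

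**Step 3: which outcomes are exposed.** Setting the Safety section beside the secondary outcome sections:

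- Relapse appears only under Safety, so it belongs to the all-treated population.
- Disability worsening and T1-enhancing and new or enlarging T2 lesions appear in both places, so they fall under both populations.
- T2 lesion load, brain volume, SDMT change and the immune outcomes are set out only in the secondary sections, so as specified measures they have only the per protocol analysis.

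**The case against.** Much of the opposing case stands.

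- **Safety is covered.** Whether the treatment worsens the disease is a safety question, and the measures that answer it are listed under Safety and go to all treated patients. A reader might infer that relapse results are also biased. They are not: relapse is not among the listed secondary outcomes.
- **The loss of patients is inferred.** A reader might take it as stated that patients who miss injections leave the per protocol set. The article gives no such rule. It is the usual meaning of the term, and the full protocol or SAP may define it otherwise.
- **The stopping trigger is not disease activity as such.** The rule speaks of significant risk. For relapse, the same section allows steroids and does not call for treatment to stop. The link between exclusion and outcome is plausible, not written.
- **Two populations are not a contradiction.** One variable can serve as a safety measure in all treated and as an efficacy measure per protocol. That is a common layout. What is missing is a statement of which result leads.
- **The work is exploratory.** No confirmatory testing is planned, p-values are to be read with caution, and dose escalation does not depend on the per protocol set.

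Two things limit this defence. The Analysis section describes the safety analysis as AE incidence, laboratory values and vital signs. It is therefore not certain that EDSS and lesion counts will be summarised for all treated in a form comparable to the secondary analysis. The section also says that conclusions will draw on all of the patient evidence, which sits badly with a single restricted set for every secondary outcome.

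**Conclusion.** The concern holds in conditional form. The article itself fixes per protocol as the only named population for the secondary and any tertiary outcomes. This is a stated choice, not a detail left to the SAP. At 9–15 patients, one or two outcome-related exclusions raise the progression-free proportion by about 6 to 19 points, assuming 3 progressors. The expected shift ranges from 0, when exclusion is unrelated to outcome, to about 20 points under the strongest selection considered. These sizes rest on assumed progression and exclusion rates and on the usual meaning of per protocol.

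The documents do not support the stronger claim that the plan will bias its results. They also do not support extending the point to relapse or to the primary safety analysis. Severity is should-fix: the analyses are exploratory, but they feed proof of principle and the choice of dose and route.

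**What to change.** In the Analysis section, make all patients who received at least one dose the main population for the secondary disability, MRI, quality-of-life and immune outcomes. Use every available scheduled assessment, whether or not treatment continued. Keep per protocol as a labelled sensitivity analysis. This also settles which result leads for the disability and lesion variables that are both safety and secondary outcomes.

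The change is mainly one of wording. Stopped patients remain under observation ("patients will still be monitored for safety issues for the duration of the study"), and the planned mixed models for repeated measurements can use patients with incomplete series. That follow-up is described as safety monitoring, so immune samples after stopping may be fewer, and available data would be used.

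There are two costs. Results may look slightly less favourable, and immune effects may be diluted by incompletely treated patients. The per protocol sensitivity analysis would show the latter.
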